### List of all SARs and safety report

For the duration of the clinical trial, the sponsor must submit to the Member States concerned **once a year or upon request**, a list of all suspected cases of serious adverse drug reactions (SARs) that have occurred during the trial as well as a report on the safety of the subjects (Development Safety Update Report, **DSUR**).

### Measures to protect against an imminent danger

Where the safety of subjects is compromised and measures are taken by the Sponsor and the investigator to protect them from immediate danger, the Sponsor immediately informs the Member States concerned about these measures and the circumstances that trigger them.

## 7.4 DATA SAFETY MONITORING BOARD (DSMB)

An external and independent DSMB will be established to monitor and protect patient safety throughout the clinical trial, with an emphasis on progress, safety data and critical efficacy endpoints of the clinical study according to the DAMOCLES group.

To detect safety signals in a timely manner, the board members of the DSMB will be instructed to perform safety analyses after 65 and 130 included patients (if there are safety issues, the DSMB may ask for a higher frequency). They will evaluate dropout rate, inclusion rate, rate of

primary out-come and SAEs. SAEs and primary outcome will be analyzed according to the randomization sequence.

The DSMB may suggest stopping the trial if the overall pattern of related SAEs supports a major safety signal, such as:

- >80% of all the participants experience SAEs (CTCAE >Grade 3 or severe/medically significant) and >80% are in the intervention group.
- >80% of all the participants experience a clinically significant infectious disease as defined by the primary endpoint and >80% are in the intervention group.
- >30% of all the participants experience a clinically significant allograft rejection as defined by the primary endpoint and >80% are in the intervention group.
- >70% of all the participants experience an allograft rejection in the 12-month protocol biopsy as defined by the secondary outcome, and >80% are in the intervention group.

Analysis of the DSMB will stratify according to sex for early detection of sex related risks.

For this trial, no statistical stopping rules will be used.

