### **Specific measures to reduce participant risk during the trial have been implemented:**

- Immunological high-risk patients will be excluded.
- TAC related AE will be assessed rigorously throughout the trial.
- An independent DSMB (Data Safety Monitoring Board) will regularly check whether predefined safety margins, sample size assumptions and rates of recruitment and loss to follow-up are met, as well as whether the level of data quality and protocol compliance is sufficient. For details see 7.4.

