### 3.5 SAMPLE SIZE

**A total of 260 patients will be included in the trial, 130 of them in the active group and 130 in the control group.**

For the sample size calculation, we analysed the occurrence of the primary endpoint (infection, allograft rejection, death and graft loss) in recipients of a kidney allograft transplanted between 1.1.2012 and 31.12.2018 at the Vienna centre, applying the trial-specific inclusion and exclusion criteria (unpublished data). Overall, 40% of patients experienced the primary endpoint between month 3 and 12 after transplantation.

An inclusion of 260 recipients will give a power of >90% to demonstrate non-inferiority with respect to the primary endpoint (assuming a decrease from 40% to 30%) using a one-side significance level of alpha 2.5%, given a 1:1 randomisation ratio. If the differences are larger, there is also sufficient power to demonstrate superiority. More details are given in section 10.

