## 6.2 REGISTRATION/RANDOMIZATION

Participants will be allocated at a ratio of 1:1 using random permuted blocks with variable block size, stratified by recruiting centre. Eligible patients will be randomized 1:1 to either

- Torque Teno virus-guided immunosuppression (arm T) or
- Standard dosing (arm S).

eCRF-based randomisation will be used. Patients will be registered at screening.

Randomization occur at visit 1 (post-transplant month 4) after confirming the inclusion/exclusion criteria. Randomization list will be created via the program nQuery-Advisor® and included in the eCRF. Implementation according to the allocation sequence will be performed by the trial personnel.

Randomization will be conducted only if the patient can be included in the study (checking of inclusion- and exclusion criteria, written consent of the patient).

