### *Allograft biopsy*

If patients have an allo-graft biopsy or receive rejection treatment outside the trial centre, the treatment centre should be contacted. The local trial team should strive to acquire all relevant documentation. To ensure this, each patient will receive an ID card with a reminder to follow these procedures and contact details of the trial centre.

Indication biopsies will be evaluated by applying standard center methodology (including HE, PAS, Trichrom, S/AFOG, silver stain and IHC). For protocol biopsies at month 12 additional molecular evaluation will be performed by the Molecular Microscope Diagnostic System (MMDx) at the Alberta Transplant Applied Genomics Centre (ATAGC, University of Alberta, Edmonton, AB, Canada). For this purpose 5 mm biopsy material will be separated, fixed in RNA-later in RNase-free cryotubes and shipped. Details concerning sampling, preparation, storage and shipping of protocol biopsies is described in a dedicated manual.

A biopsy is only counted as protocol, if, at this time point, no clinical signs of rejection are observed. Protocol biopsies are not mandatory, but data concerning month 12 protocol biopsies will be obtained if performed. Some centers have incorporated protocol biopsies in their clinical standard (at month 12 after transplantation in Vienna, Regensburg and Dresden).

All episodes of allograft biopsy will be assessed in addition by personnel blinded to the randomization code (two pathologists) following predefined protocols based on current guidelines (Banff 2019 Kidney Meeting Report published by the American Society of Transplantation). For this purpose, histological slides of graft biopsies will be scanned and sent to the evaluator via Cy-

tomine. In order to facilitate centralized assessment information concerning DSA, BK viraemia and date of transplantation and biopsy have to be provided.

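### As worded, three of the four example DSMB safety signals cannot be met under 1:1 allocation, and the fourth needs a gap above 36 points

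*Protocol*

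**What the plan says.** Protocol section 7.4 asks the board to "perform safety analyses after 65 and 130 included patients". It then lets the DSMB recommend a stop when the whole picture of related SAEs points to a major signal, and gives four examples:

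- SAEs: ">80% of all the participants experience SAEs (CTCAE >Grade 3 or severe/medically significant) and >80% are in the intervention group".
- Infection: ">80% of all the participants experience a clinically significant infectious disease as defined by the primary endpoint and >80% are in the intervention group".
- Clinical rejection: the same form, with more than 30% of all participants.
- Protocol biopsy: ">70% of all the participants experience an allograft rejection in the 12-month protocol biopsy as defined by the secondary outcome", again with more than 80% in the intervention group.

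The section adds that no statistical stopping rules apply. Section 1.3.1 lists among its risk-reduction measures that the DSMB "will regularly check whether predefined safety margins" are met. Section 6.2 states: "Participants will be allocated at a ratio of 1:1 using random permuted blocks with variable block size, stratified by recruiting centre". Section 3.5 gives the arm sizes: "A total of 260 patients will be included in the trial, 130 of them in the active group and 130 in the control group". Section 6.17 (Allograft biopsy) makes protocol biopsies optional and names the centres that have them as standard: "at month 12 after transplantation in Vienna, Regensburg and Dresden".

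**The concern.** Each example sets two conditions, and with equal arms the two restrict each other. The higher the overall event rate, the smaller the share of affected participants that one arm can contribute. At overall rates of 70% or 80%, an 80% share for one arm is more than that arm can hold.

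This matters because the protocol presents these margins as a safeguard in a strategy that, by its own account (section 1.3.1), no interventional study has tested. Section 6.23 makes a DSMB safety signal a possible reason to end the trial and refers to section 7.4 for details. The four bullets are the only place where such a signal is given numbers. The limits in section 6.16.1 define events in single patients, not margins for the trial. Margins that cannot be reached may reassure ethics committees, investigators and the board without cause.

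**Working it through.** The protocol gives no operating characteristic for these signals, so there is no stated figure to reproduce.

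**Inputs.** Allocation 1:1 (6.2); 130 per arm (3.5); reviews at 65 and 130 included patients (7.4); overall thresholds 80%, 80%, 30% and 70%, each with an intervention share of 80% (7.4).

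**Plain reading: 80% of the affected participants are in the intervention arm.** Let r be the overall rate and s the intervention share of affected participants. With equal arms:

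- intervention rate = r·s / 0.5 = 2rs
- control rate = 2r(1 − s)
- gap = 2r(2s − 1)
- a signal is attainable only if 2rs ≤ 1; at s = 0.8 this means r ≤ 0.5 / 0.8 = 62.5%

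| Signal | r | Intervention rate must exceed | Control rate at boundary | Largest possible intervention share (0.5 / r) |
|---|---|---|---|---|
| SAE | 0.80 | 2 × 0.80 × 0.8 = 128% | 32% | 62.5% |
| Infection | 0.80 | 128% | 32% | 62.5% |
| 12-month biopsy, all participants | 0.70 | 2 × 0.70 × 0.8 = 112% | 28% | 71.4% |
| Clinical rejection | 0.30 | 2 × 0.30 × 0.8 = 48% | 2 × 0.30 × 0.2 = 12% | 100% (not limiting) |

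For rejection the gap is 48 − 12 = 36 points at the boundary, and it grows with r and with s.

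**Whole-number check.** All pairs of event counts were enumerated for arm sizes 33/32, 32/33, 65/65 and 130/130. No pair meets the SAE, infection or biopsy signal. The smallest gaps that meet the rejection signal are:

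- 33/32: 17 v 4, 39.0 points
- 65/65: 33 v 8, 38.5 points
- 130/130: 64 v 15, 37.7 points

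**Unequal arms.** The SAE and infection signals first become possible with 43 of 65 or 85 of 130 patients in the intervention arm, which permuted blocks stratified by centre make practically impossible. The biopsy signal over all participants needs 37 of 65 or 74 of 130, with rejection in every one of those intervention patients.

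**Sensitivity of the rejection signal.** The protocol gives no separate rejection rate, so the rates here are assumptions. Exact binomial probability that the signal is met:

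| Intervention v control | 33/32 | 65/65 |
|---|---|---|
| 30% v 10% | 0.4% | 0.01% |
| 40% v 10% | 7.0% | 2.3% |
| 50% v 10% | 33% | 31% |
| 60% v 10% | 69% | 79% |

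For scale, the non-inferiority margin on the composite endpoint is 10 points (10.2).

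**Biopsied patients as denominator.** Affected intervention patients must exceed 0.70 × 0.80 = 56% of those biopsied, so the signal is attainable only if more than 56% of biopsied patients are in the intervention arm.

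**Second reading: 80% of the intervention arm.** The intervention rate cannot exceed 100%, so an overall rate above 80% forces a control rate above 2 × 80 − 100 = 60%. Above 70% overall, it forces control above 40%. At 81% intervention and 85% control, the overall rate is 83% and the SAE and infection signals are met with control worse. For rejection, more than 80% in the intervention arm already gives more than 40% overall, so the 30% clause has no effect.

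**The case against.** The strongest defence is that the bullets are illustrations. The lead-in is permissive and refers to the overall picture. The board sees SAEs and the primary outcome by arm, stratifies by sex and may ask for more frequent reviews. Section 6.23 lists unacceptable risks and toxicities as a separate reason to stop. This stands. A reader might infer that the safety monitoring cannot detect harm, or that no excess in the TTV arm could satisfy section 7.4. The documents do not support that: no bullet has to be met before the DSMB acts, and the rejection example can be met by a very large excess.

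The wording is also open to other readings. Besides the second reading above, the 80% could refer to SAE counts with repeats. With all 130 intervention patients and 79 controls affected (209/260 = 80.4%) and one SAE per affected control, more than 4 × 79 = 316 intervention SAEs suffice, about 2.4 per patient. But the bullets count participants, so this fits the words poorly. That the text allows several readings is itself a reason to rewrite it.

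Two further inferences do not hold. Optional biopsies do not make the biopsy signal doubly impossible: counting only biopsied patients loosens the constraint, because those patients need not split equally by arm. Nor can it be said that no patient will have reached month 12 by the second review. That follows under uniform 12-month recruitment, but the synopsis (Trial Schedule) allows 18 to 24 months. With uniform accrual, an assumption, about 10 (18 months) or 40 (24 months) of the 130 would then have passed week 36. Whether reviews should follow accrued follow-up instead of inclusions is a separate design choice, and this point does not rest on it.

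**Conclusion.** The point holds as a defect in the listed thresholds. On the plain reading with equal arms, the SAE, infection and 12-month biopsy signals cannot be met, and the rejection signal is met only at a gap above 36 points. On the reading by arm, the signals can be met but do not distinguish harm in the intervention arm from similar or worse rates in control. No reading that fits the words gives a useful comparison.

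The result assumes near-equal arms at each review and, for the biopsy signal, the stated denominator of all participants. It leaves the primary analysis, type I error and sample size untouched, and DSMB discretion remains. It should be fixed because the only numerical trial-level margins in the protocol give the DSMB no usable guidance.

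**What to change.** Replace the four bullets in section 7.4 with arm-specific event rates, or with a between-arm difference or ratio and its confidence limit. State the denominator for each signal; for the biopsy signal, use patients biopsied. Say whether patients or events are counted. Leave the threshold values to the DSMB charter, and check there that each can be reached at the 65- and 130-patient reviews. Keep the statement that the examples are non-binding, and align section 1.3.1 with the new text. The cost is protocol and charter wording.

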## 7.5 CONTRACEPTION

Human data show that tacrolimus crosses the placenta. Nevertheless, limited data from organ transplant recipients show no evidence of an increased risk of adverse reactions on the course and outcome of pregnancy under tacrolimus treatment compared with other immunosuppressive medicinal products. However, cases of spontaneous abortion have been reported. Therefore, specific measures of contraception need to be taken in this clinical trial.

Women of childbearing potential (WOCBP) are generally excluded from participation in this clinical trial except if they fulfil one of the criteria mentioned in the exclusion criteria section (4.3 Exclusion criteria, p. 29). WOCBP can be included in this clinical trial if a highly effective contraceptive measure (Pearl Index < 1% per year) is used regularly and correctly. Such methods include combined (oestrogen and progestogen containing) hormonal contraception and progestogen-only hormonal contraception associated with inhibition of ovulation, intrauterine device (IUD), intrauterine hormone-releasing system (IUS), bilateral tubal occlusion, vasectomised partner, or sexual abstinence. For male participants with a pregnant or non-pregnant WOCBP partner contraception (condom) is recommended in order to avoid exposure of an existing embryo/foetus. Contraception should be continued until the end of the clinical trial (visit 7) in WOCBP.

## 7.6 DEALING WITH PREGNANCIES

Pregnant and breastfeeding women are generally excluded from participation in this clinical trial.

The occurrence of pregnancy during the trial itself (including partners of male study subjects who become pregnant) should not be treated as an adverse event, but must be reported by the trial site to the sponsor (or its designee(s)) immediately upon becoming known. The pregnancy must be monitored and documented throughout its course. The Sponsor provides a form for this purpose. The **trial therapy has to be terminated prematurely** (see 6.21).

Further treatment as well as follow-up observation must be carried out in consultation between the investigator and sponsor, if necessary with the involvement of the treating gynaecologist. The consent of the subject is required for the involvement of the gynaecologist. The investigator shall coordinate this.

Pregnancy complications and elective terminations for medical reasons must be reported as an AE or SAE. Spontaneous abortions must be reported as an SAE.

All study materials (completed, partially completed and empty CRFs) will be retained. Data will be collected to the point of withdrawal and used for the intention-to-treat analysis if subject consent. Further visits and trial specific procedures will be continued if subject consent: in the event of premature termination of the trial therapy, the documentation of all subsequent visits should still be pursued. There will be no replacement of withdrawn subjects. The subjects may request that from the time point of withdrawal no more data will be recorded and that all biological samples collected in the course of the study will be destroyed. The PIs will take care, that the patient will receive routine post-transplant care after withdrawal.

### 7.6.1 PREGNANCIAL COMPLICATIONS AND ABORTIONS

In contrast to the onset of pregnancy itself, serious complications occurring during pregnancy while taking an IMP as well as congenital anomalies or birth defects must be documented as serious adverse events (SAEs) and reported to the sponsor in accordance with the protocol.

Any SAE occurring in association with a pregnancy brought to the Investigator's attention after the subject has completed the study and considered by the Investigator as possibly related to the investigational product, must be promptly reported to the Investigator/sponsor including the first 12 months after birth.

The sponsor is responsible for fulfilling the legal reporting obligations if an AE with a suspected causal relationship to the investigational product occurs.

AEs include:

- premature termination of pregnancy, induced or spontaneous (note: termination of pregnancy for social reasons is not subject to reporting)
- complications during pregnancy
- an unhealthy or dead child and/or
- abnormal development of the child in the first 12 months after birth

If the evaluation shows that this is a suspected case of an unexpected serious adverse reaction (SUSAR), this case must be reported in accordance with the legal requirements.

The annual Development Safety Update Report should also report positive and negative experiences during pregnancy or lactation, if relevant.

### 7.6.2 STORAGE OF DOCUMENTATION

The original reports on the occurrence and outcome of pregnancy under exposure to an IMP are stored in the ISF and copies are stored in the TMF.

## 7.7 IN-VITRO DIAGNOSTIC MEDICAL DEVICE (IVD)

The used IVD TTV R-GENE® (bioMérieux) is CE certified and will be applied according to the intended use. The laboratories will measure the TTV-Level exactly as it is described in the corresponding data sheet. The manufacturer is responsible for the legally required market surveillance and the associated vigilance monitoring and reporting.

## 8 DOCUMENTATION AND DATA MANAGEMENT

### 8.1 DELEGATION LOG OF THE TRIAL SITE

The investigator is responsible for conducting the clinical trial in accordance with the GCP guidelines, the national and EU regulatories, and the trial protocol and that the data are properly documented. It must be ensured that all data relevant to the protocol are collected only by appropriately authorized persons. The authorization of these persons and their scope of authorization is carried out by the investigator at the trial site via an authorization list (Delegation Log/ Site Signature Log), which is stored as an original in the ISF and as a copy in the TMF. It must also be ensured that the signatures and abbreviations can be clearly assigned to the authorized persons.

### 8.2 SUBJECT IDENTIFICATION LOG

Subjects included in the trial are noted in a special subject identification list at the trial site. This list must guarantee a clear assignment of the subject to the subject trial number.

The subject identification list must be kept confidential and remains at the trial site after completion of the trial. In addition, the participation of the subject in this clinical trial must be recorded in the subject record (including IMP, subject number/randomization number, start and end of the trial, contact person within the trial site).

### 8.3 INVESTIGATOR SITE FILE (ISF)

An Investigator Site File (ISF) is provided to the trial site by the sponsor. All documents required for the clinical trial are kept at the ISF, in particular the essential documents according to ICH-GCP, such as the protocol, a sample of the subject informed consent form, the authorization of the clinical trial according to the Regulation (EU) No 536/2014, and other forms must be used. Changes or the use of own templates can be made in consultation with the sponsor.

The trial site is responsible for the actuality and completeness of the ISF. This will be checked during monitoring in accordance with the regulations.

After completion or discontinuation of the trial, the ISF must be retained for at least 25 years.

### 8.4 CASE REPORT FORM

Data relevant to the trial protocol is documented in the electronic Case Report Form (eCRF) specially created for this trial.

In addition to the investigator, only persons authorized by the investigator are granted access to the eCRF. The access data may not be passed on to third parties. The scope of authorization and the associated rights in the eCRF are controlled by data management via appropriately defined user roles.

The data relevant to the trial protocol (including the data of trial subjects who were prematurely excluded from the trial) must be documented in the eCRF pseudonymously, promptly, legibly (without the use of abbreviations), completely and in accordance with the source data.

Implausible values, which are displayed during data entry by programmed checks, must be checked by the trial site and corrected if necessary. If a correction is made in the eCRF, the reasons for it must be given. By means of the audit trail, all data and corrections are

automatically logged with date, time and the user name of the person entering the data. All old entries are retained and can be retrieved at any time.

A paper-based interim CRF is provided to the trial site as part of the ISF. This enables timely documentation in accordance with the protocol if the eCRF is not available (e.g. due to a system malfunction). The authorized persons will transfer the data immediately from the interim CRF to the eCRF as soon as the fault has been rectified.

The correctness and completeness of the documentation is confirmed by the authorized persons after each visit to the eCRF. Once the documentation for a subject has been completed, the principal investigator finally confirms the documentation for this subject in the eCRF.

Queries by the sponsor or its representatives must be checked by authorized persons using the source data and answered directly in the eCRF. Any resulting corrections must be made in the eCRF.

